## **BedMed-Frail: Does the potential benefit of bedtime antihypertensive prescribing extend to frail populations?**

---

**OVERVIEW:** The BedMed trial (led out of the U of A and funded by both Alberta Innovates Health Solutions, and the Canadian Institutes for Health Research) is a pragmatic multi-provincial trial intended to determine whether bedtime antihypertensive use, as compared to conventional morning use, reduces major adverse cardiovascular events in community dwelling primary care patients. BedMed-Frail, led by the same group of investigators, is a complementary but separate randomized trial evaluating whether the risks and benefits of bedtime antihypertensive use differ in a long-term care (LTC) population. To accomplish this, BedMed-Frail randomizes residents in participating Alberta LTC facilities to the antihypertensive medication timing intervention (i.e. bedtime versus conventional morning use) and draws both trial outcomes and baseline covariates from routinely collected electronic health data – using both administrative claims data and the Resident Assessment Instrument Minimum Data Set (RAI-MDS).

**PURPOSE:** To determine the optimal time of day for blood pressure lowering medication to be administered to long-term care residents.

**HYPOTHESIS:** Bedtime administration will result in fewer adverse health events.

### **JUSTIFICATION:**

**A) THE BURDEN OF HYPERTENSION:** In Canada cardiovascular disease (CVD), most notably stroke, heart attack (MI), and congestive heart failure (CHF) accounts for 1 in 3 deaths, and 1 in 6 hospitalizations. Hypertension (high blood pressure), a modifiable risk factor present in 1 of 5 Canadian adults, is the leading cause of stroke and predisposes patients to heart attack, congestive heart failure, kidney disease and dementia. Using population-based Canadian administrative data (2002 - 2010), it was recently estimated that Canadian healthcare costs attributable to hypertension were \$13.9 billion in 2010 and projected to rise to \$20.5 billion in 2020. If high blood pressure (BP) can be reduced in a way that is more effective at preventing these life threatening and potentially disabling conditions, better health outcomes and substantial cost savings are possible. One way to improve the effectiveness of BP medications may be to administer them at bedtime.

**B) THE OPPORTUNITY BEDTIME PRESCRIBING MIGHT PROVIDE (the “MAPEC” trial):** Blood pressure (BP) normally exhibits a circadian rhythm with relatively lower pressures during sleep. Lack of this sleep time “dip” correlates strongly with adverse cardiovascular events and BP correlates most strongly with such events when measured at night (i.e. during sleep). Motivated by such observations, Spanish researchers studied the effect of taking BP medication at BEDTIME (when the effect on nighttime BP would be greatest) versus conventional morning use, when most BP medications (meds) are taken. The results of this study (the MAPEC trial) were striking. Over a median 5.6 years follow-up, adverse cardiovascular events occurred in 187 of 1084 subjects taking BP medication in the morning but only 68 of 1072 subjects who took their BP medication at bedtime (relative risk 0.39, 95%CI [0.29-0.51],  $p < 0.001$ ). This 61% reduction in adverse events was similar for all individual components of the primary outcome (including death from all causes, stroke, MI, new angina pectoris, CHF and retinal artery occlusions). If true, a switch to bedtime prescribing would have more impact on the health of hypertensive Canadians than whether high BP is treated at all. And yet this trial failed to change practice. This is because replication of such surprising results is required for these findings to be believed – primarily because the benefit seems “too good to be true”, far exceeding

all other methods of CVD risk reduction (e.g. high dose statins convey a 35% relative risk reduction, morning BP meds 30%, exercise 25%, aspirin 15%).

**C) OTHER STUDIES IN HUMANS:** Neither Oct 2013 literature review, 2011 Cochrane systematic review, nor our more current (2018) search of the literature, found any RCTs (besides MAPEC) evaluating the effect of BP medication timing on mortality/morbidity. Other trials look only at 1) how medication timing affects BP (not cardiovascular events), or 2) compare AM vs. bedtime use of differing drug classes. **1) Effect on BP:** Clearly, except for dihydropyridine calcium channel blockers such as amlodipine whose BP lowering is largely independent of administration time, medications from every antihypertensive class (when taken at bedtime instead of AM) will preferentially lower overnight BP. **2) Comparing AM vs. bedtime use of different drug classes:** A 2014 review identifies 5 such RCTs and attempts to combine them in meta-analysis. Although the authors report overall benefit to bedtime prescribing it is difficult to see how such disparate trials could be meaningfully combined. Two of these studies also found no difference - although one (FACET) was a trial of morning fosinopril versus evening amlodipine (which doesn't preferentially lower overnight BP) and the other (CONVINCE) was a trial of morning BP meds (atenolol or HCTZ) vs. evening controlled onset delayed release verapamil, which releases upon waking each morning (i.e. it was NOT a trial of overnight BP lowering).

**D) ANIMAL STUDIES:** In an examination of 12 mouse organs, 43% of all protein coding genes showed circadian rhythms in transcription - with transcription "rush hours" typically preceding dawn or dusk. This includes genes such as VEGF (vascular endothelial growth factor) that regulate angiogenesis. Conceivably, elevated BP at night and elevated BP during the day may have very different metabolic effects on a variety of tissues. Altering the time at which peak BP lowering occurs could potentially alter the benefit conveyed.

## **OBJECTIVES:**

- A) To determine if switching  $\geq 1$  BP Med to bedtime alters cardiovascular outcomes.
- B) To determine if switching  $\geq 1$  BP Med to bedtime alters behavior outcomes.
- C) To determine differences in acute care costs between morning and bedtime users.

## **RESEARCH METHOD/PROCEDURES:**

**A) SETTING:** Alberta is home to the Institute for Continuing Care Education and Research (ICCER), a network of long-term care facilities intent on providing new knowledge relevant to improving quality of care for their residents. Working with their Executive Director ([name]) the BedMed investigators have approached, and obtained, support for BedMed-Frail from multiple ICCER-affiliated LTC organizations. Currently this includes the Bethany Care Society, Capital Care, Shepherd's Care, Sherwood Care, Wingkei, and Lifestyle Options Retirement Communities. Other facilities might join in before randomization begins. Collectively these facilities would have approximately 1200 eligible residents during the 2-3 year study period.

**B) DATA SOURCE:** All our outcomes and baseline covariates are derived from routinely collected electronic health data. This includes Ministry of Health / Health Authority administrative claims data (physician billings, vital statistics, emergency and hospital separations, prescriptions dispensed) and quarterly clinical care data captured by all LTC facilities in the Minimum Data Set (MDS) which is recorded quarterly in all institutions for all residents. To access and analyse this data (both administrative claims and MDS) we are partnering with the Alberta SPOR Data Platform through [name] (*Senior Biostatistician, Patient Health Outcomes and Clinical Effectiveness Unit, Alberta Health Services*) and his team of AHS biostatisticians.

## **C) BEDMED-Frail TRIAL PROTOCOL:**

**Design:** Event-driven Prospective Randomized Open Blinded End-Point (PROBE) Randomized Trial.

**Population:** Hypertensive long-term care (LTC) residents using BP lowering medication.

**Inclusion Criteria:** 1) Hypertension diagnosis as indicated by  $\geq 2$  such billing diagnoses at any time in the administrative claims data by any provider; 2)  $\geq 1$  ONCE DAILY BP lowering medication; 3) LTC resident in a participating facility.

**Exclusion Criteria:** 1) Personal history of glaucoma or use of glaucoma medications. *Glaucoma is an exclusion because nocturnal hypotension (i.e. excessively low blood pressure while sleeping) has been associated with ischemic optic neuropathy in such patients.* 2) Any family member or treating physician (all of whom will be notified of the LTC facilities participation in this initiative) requesting the patient not participate.

**Intervention:** Switching (*one at a time as tolerated*) one or more morning BP meds to BEDTIME (or *maintaining* bedtime BP meds if already taken at that time). The timing of loop diuretics (which can cause meaningful diuresis), and BP medications taken more than once a day, will not be altered. If more than one medication change is needed, each change will take place one week apart.

**Comparator:** Maintaining (or switching to) morning BP medication use.

**Outcomes:** Outcomes are drawn from administrative claims data and quarterly MDS reporting. The Alberta SPOR Data Platform will monitor our primary outcomes quarterly during the trial, and the trial will conclude once 301 participants have experienced primary outcome events. Outcomes include:

- Primary: Composite of all-cause death and hospital admission or emergency room visit for acute coronary syndrome/MI, heart failure, or stroke (using administrative data based case definitions with validated coding algorithms).
- Secondary: 1) Each element of the primary outcome alone; 2) All-cause hospitalization; 3) Acute Care Costs (from each admissions resource intensity weight & length of stay).

*The following additional outcomes (unless otherwise indicated) will be determined from the first available **MDS Quarterly assessment** in the 3 - 6 month window post randomization:*

- Safety: 1) Fell (past 30 days); 2) Any Fracture (from administrative claims data over the study duration – not MDS data); 3) Full Thickness Skin Ulceration (stage 3 or 4).
- Tolerability: Bladder Continence.
- Process: 1) % of once daily BP medications taken according to allocation (via hand audit of medication records 6 months post date of randomization); 2) Number of once daily BP medications 6 months post date of randomization (via administrative claims data). 3) Number of BP medications taken more than once daily.
- Exploratory (Cognitive / Behavioral): 1) Deteriorated cognition relative to status 90 days prior; 2) Receipt (last 7 days) of a) Antipsychotic Medication, b) Antianxiety Medication, c) Hypnotic Medication, d) Physical Restraints; 3) Behavioral symptoms that are present a minimum of 4 days per week and not easily altered including a) Wandering, b) Verbal Abuse, c) Physical Abuse, d) Socially Inappropriate or Disruptive Behaviour, e) Resisting Care; 4) Indicators of Depression or Anxiety Almost Daily (last 30 days).

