#### **D) Power/Sample Size Estimate:**

Expected Recruitment: At the time of this application we are collaborating with multiple ICCER-affiliated LTC organizations that wish to participate in this initiative. Most of these organizations have multiple facilities, many of which have multiple buildings or wings. Using Canadian Primary Care Sentinel Surveillance (CPCSSN) EMR data (accessed for the purpose of this application) we know that 53% of Canadians 80 yrs and older are listed as currently taking daily BP lowering medication. In our experience most of these medications are maintained upon nursing home admission. This suggests, given the 18-month median lifespan of newly admitted patients (and 9 month median lifespan of those already resident at the time of the study), that we should easily obtain 1200 residents total over the roughly 2-3-year duration of the trial.

Power: Utilizing well described methods for sample size determination, inflating the number of events to account for noncompliance, conservatively setting the median lifespan at 3 years to account for the inclusion of supportive living residents who, on average, live longer than the expected 18 months in long-term care facilities and assuming 33% of patients will be censored prior to any events, we find that 1232 patients would have 80% power (at a p of 0.05) to detect a difference between groups in the primary outcome of 27.6%. Although smaller differences would still be clinically meaningful, this difference is less than the 55% relative reduction in total mortality claimed in the MAPEC trial that we are trying to reproduce, and it is a very conservative minimum estimate for the actual power that the study will have. Additional power, while not directly calculable, will come in 2 ways: 1) These calculations assume no meaningful covariates and we have several covariates that are likely to be predictive of each outcome – in particular the resident's

level of care designation, and 2) we will continue to seek new facilities to partner with over the course of the trial – which should increase the number of residents available.

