| 21-03-2022 | 22-03-2022 | Change in study coordinator contact information on documentation.                                                                                                                                                                                                                                                                                                                                                                                                                                                                                                                                                                                                                                                                                                                                                                                                                                                                                                                                                                         |
| 24-01-2023 | 30-01-2023 | A new process is being added: AHS and Alberta Health administrative data will be utilized between April 2002 and December 2025 for the purpose of determining patient characteristics and outcomes. Specifically, PIN will be used to determine Blood Pressure medication timing in the 30 days before randomization up to 6 months post randomization by using the medication instructions held within PIN using appropriate keyword searches.                                                                                                                                                                                                                                                                                                                                                                                                                                                                                                                                                                                           |

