# BedMed-Frail Statistical Analysis Plan

## **Adaptive Randomization (conversion to modified intention-to-treat)**

Participating facilities are volunteering to support our trial with no financial compensation, and “fitting it in” with other work. For several facilities, COVID-19, other infectious outbreaks, and implementation of other facility initiatives has led to long delays before the facility pharmacist was able to act on their allocation list. For a few facilities this delayed implementation by several months. Given 1) we are placing an equal emphasis on detecting harm, 2) long implementation delays make both groups look more similar and reduce the ability to detect harm, and 3) no action of any kind was taken related to the facility’s allocation list in this interval, we have adapted the trial to consider the date of each facility’s initial randomization to be the date the allocation list was actually acted upon, and not the date it was generated. This date was determined by the AHS data analyst, using electronic pharmacy dispensing data, to be the day before the first switch of an eligible patient’s BP medications from morning to bedtime. Individuals who, on the date of implementation, were no longer resident in the facility, hospitalized, or without once daily BP meds, were excluded from the trial.

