### Subgroup Analyses

We will repeat the primary outcome analysis for those with and without the following baseline characteristics: Male sex, resistant hypertension (defined as ≥ 3 antihypertensive medications), CHF, CKD, diabetes and (separately) use of the major BP medication classes (ACEI, ARB, CCB, diuretic, beta-blocker).

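### Residents already on bedtime dosing are eligible, the documents disagree on whether such controls move to morning, and no planned analysis separates them

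*Combined protocol and SAP*

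**What the plan says.** **Eligibility.** The protocol's inclusion criteria (section C) ask for at least one once-daily BP drug and say nothing about when it is given. The SAP repeats the check at its revised randomization date: residents "no longer resident in the facility, hospitalized, or without once daily BP meds, were excluded from the trial". Timing is again not a criterion.

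**Intervention arm.** Morning drugs are moved to bedtime, or the arm consists of "maintaining* bedtime BP meds if already taken at that time".

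**Control arm.** Three places bear on it.
- Protocol section C, Comparator: morning use is either kept or switched to.
- Protocol, case for a waiver of consent, item 1: the only change is to the timing believed safer, and timing in the control institutions does not change.
- Amendment log, entry of 5 November 2019: under individual randomization, a single message tells the pharmacist which residents are to move to bedtime. No instruction for controls is described.

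**Objective A.** "To determine if switching $\geq 1$ BP Med to bedtime alters cardiovascular outcomes". The protocol overview describes the contrast more broadly, as bedtime versus conventional morning use.

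**Analysis.** Randomization is unstratified. Baseline timing is not in the protocol's baseline data list or in the SAP's Table 2 covariates. The SAP's Subgroup Analyses section says "We will repeat the primary outcome analysis for those with and without the following baseline characteristics" and lists ten characteristics, none of them timing. Neither sensitivity analysis uses it.

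**Data.** The January 2023 amendment states that "PIN will be used to determine Blood Pressure medication timing in the 30 days before randomization up to 6 months post randomization".

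**The concern.** A resident whose once-daily drugs are all at bedtime at baseline cannot be switched to bedtime. In the intervention arm nothing changes. In the control arm there are two possibilities, and the documents support each in a different place.

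- The resident is moved to morning. The comparison is then bedtime versus morning, reached from the other direction.
- The resident stays at bedtime. Both arms then receive the same timing, and the resident adds events but no contrast.

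In the second case the hazard ratio is pulled toward 1. Power is lost for benefit and for harm alike, and the SAP says it places equal emphasis on detecting harm. A null result would be harder to read, because no outcome analysis distinguishes residents whose timing could move to bedtime from those whose timing could not.

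The per-protocol analysis does not fill the gap. It drops facilities where bedtime doses in the intervention group are below 60%. Residents already at bedtime count toward that 60%, and bedtime use among controls is not looked at.

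**Working it through.** **Inputs.** From protocol section D: "1232 patients would have 80% power (at a p of 0.05) to detect a difference between groups in the primary outcome of 27.6"%, taken as a hazard ratio (HR) of 0.724, with alpha two-sided (sidedness is not stated) and 1:1 allocation. From section C: "the trial will conclude once 301 participants have experienced primary outcome events". Section D also mentions "inflating the number of events to account for noncompliance", without a rate. The baseline bedtime share *b* is not given. The only indication is in the waiver section, which says once-daily drugs are typically given in the morning. The values of *b* below are assumptions.

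**1. The plan's own figure (Schoenfeld).**

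Events = 4 × (1.960 + 0.842)² / (ln 0.724)² = 4 × 7.849 / 0.1043 = 301.0.

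Power = Φ(|ln HR| × √D / 2 − 1.960) = Φ(0.3230 × 8.675 − 1.960) = Φ(0.842) = 80.0%.

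The 301 reproduces with no added events. Either 27.6% is already net of noncompliance, or the stated inflation is not in the 301. The documents do not say which.

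**2. Controls moved to morning, as the Comparator line allows.** Residents already at bedtime contribute a bedtime-versus-morning contrast like everyone else. HR 0.724, 301 events and 80% power hold for any *b*.

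**3. Controls left at bedtime.** A share *b* has no contrast. The net HR depends on how the mixture is modelled, so three versions are shown:
- (i) log scale: HR = exp[(1 − b) × ln 0.724]
- (ii) hazard average, the share at HR 1: HR = (1 − b) × 0.724 + b
- (iii) the share at the bedtime hazard in both arms: HR = 0.724 / [(1 − b) + 0.724b]

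| Assumed b | (i) HR, power | (ii) HR, power | (iii) HR, power |
|---|---|---|---|
| 5% | 0.736, 75.9% | 0.738, 75.1% | 0.734, 76.5% |
| 10% | 0.748, 71.3% | 0.752, 69.7% | 0.745, 72.5% |
| 20% | 0.772, 61.1% | 0.779, 58.1% | 0.766, 63.7% |

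**4. A restricted analysis at the same data cut.** Excluding the share *b* leaves 301 × (1 − b) events at HR 0.724: 286, 271 and 241 events, with power 78.0%, 75.7% and 70.7% for *b* = 5%, 10% and 20%. If controls stayed at bedtime, this improves on step 3 (i) by about 2, 4 and 10 points and removes this source of dilution. If controls were moved, it loses power against 80%. These event counts do not allow for also removing residents whose only once-daily BP drug is a loop diuretic, a share that is likewise not given.

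**5. Interaction by baseline timing, b = 10%.** About 30 events fall in baseline bedtime users and 271 in the rest. The SE of the difference in log HR is √(4/30.1 + 4/270.9) = 0.384. Against a difference of 0.323, z = 0.84 and two-sided power is about 13%.

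**The case against.** The strongest reply is the Comparator line. It provides for switching to morning, so the protocol does say what happens to a control already at bedtime. On that reading there is no dilution. The comparison also fits the stated purpose (the best time of day), the overview's contrast and Objective C, which compares morning with bedtime users. Only the word *switching* in Objectives A and B fits badly. This stands.

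A reader might infer that the primary contrast is therefore not bedtime versus morning, or that the sizing assumed every resident would be switched. The documents support neither. The Comparator line points against the first. Section D gives only a between-group difference with a noncompliance allowance, and if 27.6% is already net, taking dilution off 80% could count it twice.

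The lack of timing information should not be overstated either. The SAP's monthly process outcomes and the protocol's audit of doses taken according to allocation will describe whether timing changed. They do not enter the outcome analysis or classify residents by baseline timing.

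It is also fair to say that the waiver wording looks like a remnant of the cluster design, that the share may be small, and that a final protocol published in 2023 is cited but not included in these documents. What the reply does not remove is the disagreement within the protocol itself, or the log's description of pharmacist messages that covers moves to bedtime only.

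**Conclusion.** The concern holds in a limited form. Residents already at bedtime are eligible, Objective A's wording does not fit them, and no planned analysis separates them. The protocol's Comparator line and its waiver section conflict on what happens to them in the control arm and must be reconciled.

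Whether power is affected depends on which was carried out. If the Comparator line was followed, the effect is nil. If control bedtime users stayed put, power is about 75–76%, 70–73% or 58–64% at shares of 5%, 10% or 20%. These figures rest on an assumed share, a true HR of 0.724 in residents who can be switched, two-sided 0.05, 1:1 allocation, and 27.6% not already being net of such residents. They show what is at risk under one reading; they are not evidence that the trial is underpowered. This is a worthwhile, low-cost improvement and not a flaw in the primary analysis.

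**What to change.** 1. Reconcile the Comparator line with the waiver section, and state what the pharmacists were told about controls already at bedtime.
2. Leave the primary analysis unchanged.
3. Add one prespecified supportive analysis of the primary and safety outcomes, by allocation, in residents with at least one once-daily, non-loop BP drug directed for the morning in the 30 days before the SAP's randomization date. Classify both arms from the PIN directions field before outcomes are seen. Loop diuretics are left out because the protocol does not alter their timing. The set is defined at baseline, so the randomized comparison within it is kept.
4. Report baseline timing by arm, and list it as a descriptive subgroup for the primary outcome.

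**Cost.** One SAP paragraph and one extra model per outcome, on data already being extracted. The restricted set has fewer events. Some residents will be misclassified where the directions are unclear. The interaction has little power (about 13% at a 10% share), so a non-significant interaction would not show that the effect is the same in both groups. For these reasons the restricted result should support the primary comparison and not replace it.

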**Baseline Data:**

- Baseline annualized rate of the primary outcome in the resident's facility (last 3 years)
- Age
- Gender
- Location (Calgary / Edmonton / Other)
- Level of Care Designation (Long Term Care, Long Term Care-Dementia, Supportive Living, Supportive Living-Dementia, Personal Supportive Living)
- Length of stay in LTC facility
  - New admission (last 60 days)
  - Old Admission ( $\geq 3$  years)
- Charlson score

- Key Comorbidities - requiring 2 claims or 1 in-hospital diagnosis (any Dx, not just primary Dx) over the duration of available administrative claims:
  - Diabetes
  - Coronary Artery Disease (CAD)
  - Stroke
  - Osteoarthritis (OA)
  - Congestive Heart Failure (CHF)
  - Chronic Obstructive Pulmonary Disease (COPD)
  - Hip Fracture – for this characteristic only 1 diagnosis is required
  - Chronic Kidney Disease (CKD) – for this characteristic only 1 diagnosis is required (since family physicians rarely have CKD dedicated visits), or 2 GFR < 40
  - Dementia
  - $\geq 2$  of the above Key comorbidities
- TIA (1 claim or 1 in-hospital Dx)
- Stroke or TIA (1 claim or 1 in-hospital Dx)
- Dialysis (1 procedure)
- Total number of medications
- Total number of BP medications
- Days in hospital in prior 6 months
- Number of ER visits in prior 6 months
- *Collected for the purpose of inclusion / exclusion*
  - *Hypertension (2 claims or 1 in-hospital) – inclusion criteria*
  - *Any once daily hypertension medication – inclusion criteria*
  - *Glaucoma – exclusion*

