3. Implementing the Intervention: Each facility's pharmacist will be in charge of implementing the intervention. The pharmacy will receive a list of eligible residents directly from the AHS biostatistician supporting the study using an e-mail with a secure link. Only once a day BP medications will be changed and the recommendation is to change BP medications in the order ABCD-O (Angiotensin Inhibitor / Angiotensin Receptor Blocker, Beta-Blocker, Calcium Channel Blocker, Diuretic, Other). If there are multiple once daily BP medications, only one timing change will be made per week. If the pharmacist is aware of any clinical reason why a particular timing would be better they will follow their clinical judgment. Patients with known glaucoma, or who use glaucoma medications, will keep to morning BP medications. A BedMed physician will be available 24 hours for pharmacist questions related to timing changes.
4. Study Follow-up: Post implementation of the intervention, the study team will monitor administrative claims and RAI-MDS data quarterly. The study will end once 301 primary outcome events have been observed.

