### Sensitivity Analyses

- 1) We will conduct a per-protocol analysis by excluding residents from any facility where fewer than 60% of medication doses are taken at bedtime in the intervention group 6-months post implementation.
- 2) We will conduct a full intention-to-treat analysis by including everyone who was initially assigned an allocation, even if they became ineligible (e.g., died) while waiting for their facility to act on the allocation list.

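### On the natural reading of the protocol, a resident whose only once-daily BP drug is a loop diuretic is eligible but has no timing contrast; the drug rules need reconciling

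*Combined protocol and SAP*

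**What the plan says.** Four places decide who is randomised and which drugs move.

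- **Protocol, Inclusion Criteria, item 2:** at least one "ONCE DAILY BP lowering medication". The matching eligibility field under Baseline Data reads "Any once daily hypertension medication". Neither mentions loop diuretics, and the only exclusions are glaucoma and an objection from family or physician.
- **Protocol, Intervention:** "The timing of loop diuretics (which can cause meaningful diuresis), and BP medications taken more than once a day, will not be altered".
- **Protocol, Recruitment / Patient Flow, Implementing the Intervention:** "Only once a day BP medications will be changed and the recommendation is to change BP medications in the order ABCD-O", where D stands for diuretic. No loop exception is repeated here.
- **SAP, Adaptive Randomization:** residents who on the implementation date were "no longer resident in the facility, hospitalized, or without once daily BP meds, were excluded from the trial".

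The SAP's two sensitivity analyses do not single out these residents. The per-protocol analysis works by "excluding residents from any facility where fewer than 60% of medication doses are taken at bedtime in the intervention group", which removes facilities, not individuals. The full intention-to-treat analysis adds residents back.

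On size, the protocol's power paragraph states that "1232 patients would have 80% power (at a p of 0.05) to detect a difference between groups in the primary outcome of 27.6" percent. The trial ends at 301 primary events. The same paragraph says that the number of events was inflated for noncompliance, without saying by how much.

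**The concern.** The Intervention paragraph names two kinds of drug that allocation leaves alone: loop diuretics, and BP drugs given more than once daily. The inclusion criterion screens out residents who have only the second kind. Nothing screens out residents whose once-daily treatment consists only of the first. Under the Intervention paragraph they keep the same timing whichever arm they are in, so they contribute events but no information on timing.

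The effect is to move the primary hazard ratio, and the rate ratios for the safety outcomes, toward 1. For harm this matters as much as for benefit. The SAP re-dated time zero because implementation delays made the arms alike and weakened the detection of harm. It wrote that change for facility-wide delays, but a resident with no movable drug dilutes the comparison in the same way, and for the whole of follow-up.

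The protocol's first two objectives also concern switching at least one BP drug to bedtime, which in these residents the Intervention paragraph does not allow.

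**Working it through.** **1. Do the texts leave the gap?** Take a resident with a hypertension diagnosis, a once-daily loop diuretic and no other once-daily BP drug.

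| Text | Result for this resident |
|---|---|
| Inclusion item 2 and Baseline Data field | Eligible, if a loop diuretic counts as a BP drug |
| Intervention paragraph | Timing not altered |
| Implementing the Intervention | Diuretics are in the switching order; loop exception not repeated |
| SAP re-check at implementation | Retained, because a once-daily BP drug is present |
| SAP per-protocol analysis | Retained, unless the whole facility is dropped |
| SAP full intention-to-treat analysis | Retained |

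A resident who also takes another once-daily BP drug keeps a contrast and is not affected.

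**2. Reproduce the plan's figure.** Inputs from the protocol: 27.6% difference, read as HR = 1 − 0.276 = 0.724; p of 0.05; 80% power. Random blocks of 2 or 4 imply 1:1 allocation. The number of sides is not stated.

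Schoenfeld: D = 4 (z for alpha + z for power)² / (ln HR)².

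- Two-sided: 4 × (1.960 + 0.842)² / (ln 0.724)² = 301.0, the plan's 301.
- One-sided: 238, which does not fit.

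So 301 is the two-sided count for HR 0.724 with nothing visible on top for noncompliance. Either 27.6% is already net of noncompliance, or no inflation was applied. The documents do not say which.

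**3. Dilution.** Let g be the share of primary events from residents with no contrast. The documents give no value, so the shares below are assumptions. If 27.6% is the undiluted effect:

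- linear pooling: HR = 1 − 0.276 (1 − g)
- log pooling: HR = exp[(1 − g) ln 0.724]
- power = Φ(½√301 × |ln HR| − 1.96)

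The last column shows power if these events are dropped and not replaced, at HR 0.724.

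| g (assumed) | HR, linear | Power, linear | HR, log | Power, log | Events left | Power if dropped |
|---|---|---|---|---|---|---|
| 0 | 0.724 | 80% | 0.724 | 80% | 301 | 80% |
| 1% | 0.727 | 79% | 0.726 | 79% | 298 | 80% |
| 2% | 0.730 | 78% | 0.729 | 78% | 295 | 79% |
| 5% | 0.738 | 75% | 0.736 | 76% | 286 | 78% |
| 10% | 0.752 | 70% | 0.748 | 71% | 271 | 76% |

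Example, linear at 10%: HR = 1 − 0.276 × 0.90 = 0.7516, |ln HR| = 0.2856, and ½√301 = 8.675. Then 8.675 × 0.2856 − 1.96 = 0.517, and Φ(0.517) = 0.70.

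With log pooling, power has fallen by more than two points once g reaches about 2.5%. At each assumed share, dropping these events costs less power than keeping them. Counting 301 events among residents with a movable drug restores 80%.

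**The case against.** **The key term is undefined.** The documents never say that a loop diuretic is a BP-lowering drug. The Intervention sentence can be read as listing loop diuretics beside BP drugs, not among them. The switching order and the SAP's subgroup list say diuretic only in general. If the working eligibility list already left out loop diuretics, there is no gap. This stands as a limit. The reading used here is still the more natural one, since a BP-drug switch would otherwise need no loop exemption.

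**The implementation text could create a contrast.** A pharmacist following only that paragraph might move a once-daily loop diuretic. A reader might infer that these residents can never have a contrast; the documents do not support that, because the two paragraphs differ.

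**The final protocol was published separately.** Both supplements say so, and it may hold the operative drug list. That cannot be checked from the documents supplied.

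**The size is assumed.** A reader might infer a serious loss of power, for instance by supposing that these residents have more heart failure and a higher event rate. The documents give neither their number nor their hazard. At 1% to 2% of events the loss is one to two points.

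**Noncompliance was allowed for.** If 27.6% is already net of noncompliance, some or all of the power loss is covered. That would not undo the dilution of the estimate.

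**The design is pragmatic.** It already accepts unswitched residents through pharmacist judgement and free reversal. But those are departures from allocation after randomisation; this is an eligibility definition that can be settled beforehand from baseline data, alike in both arms.

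**Conclusion.** The point holds as an inconsistency between eligibility and intervention. On the natural reading of the Intervention paragraph, following it together with the inclusion criterion and the SAP re-check puts residents without a timing contrast into the primary and safety analyses. No planned analysis removes them as individuals. The direction is toward no difference, for benefit and harm alike.

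The size cannot be determined from the documents. The power figures above rest on assumed shares, on 27.6% being the undiluted effect, on no effect in loop-only residents, and on a two-sided test. It is a cheap improvement to the definition of the analysis set, not evidence that the trial is materially underpowered.

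**What to change.** First, the investigators should reconcile the Intervention paragraph, the implementation instructions and the SAP re-check, and define the term for a BP-lowering drug. This review takes no position on which drugs should be moved.

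Then:

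- Word inclusion item 2 and the SAP re-check as at least one once-daily BP drug whose timing the protocol allows to change. Read this from dispensing data before time zero, by the same rule in both arms.
- Count the 301 events in that set.
- Keep everyone in the full intention-to-treat sensitivity analysis.
- Report the number of loop-only residents by arm, so that readers can judge the dilution.

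If residents are already randomised and results have been seen, use the same filter as a sensitivity analysis and leave the primary set alone. The October 2024 entry in the amendment log reports outcome results, so for any analysis after that date this is the applicable form.

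The cost is a change of wording and one drug-class filter. The SAP already uses dispensing data to date implementation and already classifies drugs for its subgroups. The downside is a somewhat smaller primary set and a later 301st event, both in proportion to the loop-only share: at an assumed 10% of events, about 30 of the 301 would have to be replaced.
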